### Analysis—modelling cost-effectiveness

Ideally, the presence of an osteoporotic VF will result in formal assessment of future fracture risk and prescription of medications such as bisphosphonates. Follow-up data will allow identification of patient pathways after patients have received their spinal radiograph. This will allow estimation of the number of older women receiving new bisphosphonate (or other anti-osteoporosis medications) prescriptions and whether they had any further investigations (such as a DEXA scan) or additional primary care contacts, including physiotherapy after their radiograph. A modelling approach will be used to estimate the cost-per-quality adjusted life year (QALY) if Vfrac is implemented in the NHS. The EQ-5D data collected during this study will provide a baseline QALY for older women with back pain in the UK, as these data are not currently available. Data from the literature will be used to model the likely difference in change in QALYs between any future control and intervention arms. These will be based upon estimated changes in QALYs including, for example, due to age, occurrence of osteoporotic fracture, management of back pain and prescription of medications for osteoporosis.

Without a randomised element, it is not possible to measure the proportion of women going on to get the correct diagnosis of VF and appropriate treatment in the absence of the Vfrac tool. It is, therefore, necessary to explore alternative scenarios using expert opinion. Opinion of experts in the fields of primary care, osteoporosis and care of the elderly will be obtained on likely patient pathways in the absence of Vfrac. Interviews and group discussions will be undertaken with physicians, surgeons, GPs and allied health professionals in the fields of primary care, osteoporosis and care of the elderly over a 6-month period will provide an estimation of each likely step in the treatment pathway of women with back pain occurring in the absence of Vfrac including to estimate costs of any adverse effects of medications.

As individual-level data will be available, the uncertainty (variance) of our cost-effectiveness analysis will be estimated via a probabilistic uncertainty approach using Monte Carlo Simulations in combination with non-parametric bootstrapping techniques, where appropriate. The quality and validity of the cost-effectiveness model will be ensured by (1) basing the structure of the model on previous cost-effectiveness models in the field of osteoporosis; (2) ensuring inputs to the model are valid; (3) ensuring modelling is appropriated to the future decision-making context of Vfrac (that is, from the NHS perspective and tailored to CCGs); and (4) the uncertainty (variance) is clearly identified so it can be tested in any future pilot study.

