A total of 1633 women aged over 65 years will be recruited via primary care from two sites within England — Bristol and Stoke-on-Trent. Potential participants will be asked for their consent via post and asked to fill in a baseline questionnaire containing items on demographics, socioeconomic status, traditional risk factors for osteoporosis, back pain, quality of life, medication use, healthcare utilisation and comorbidity. Upon the study team’s receipt of the completed baseline questionnaire and consent form, an appointment will be made for the participant to have a physical examination in secondary care followed by a lateral thoracic and lateral lumbar radiographs performed using standard NHS standard operating procedure on the same day. Before the physical examination, the participant will be asked, in person, to sign another consent form. In this consent process, they will be asked if they agree to the physical examination and radiograph. The radiograph report will be sent to the participant’s general practitioner (GP) as if the GP had ordered the radiograph. The GP practices will be given a guidance document upon recruitment, providing information on recommended pathway for patients with a vertebral fracture. This advice has been taken from the North Bristol NHS Trust guidance for GP practices within BSSG CCG (Fig. 1). The first step in this guidance is an X-ray to confirm VF.

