**Fig. 2 Fig2:**
[figure not shown]
Study flowchart

The primary objective is to develop a clinical screening tool for identifying older women with back pain who are likely to have VF. The output will be a simple clinical checklist of self-reported data and data from the physical examination which will produce a binary assessment of (1) yes—this person needs a spinal radiograph, or (2) no radiograph needed. The primary evaluative measure will be the accuracy of the Vfrac tool as represented by the sensitivity and specificity of > 80%.

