### Objectives and outcome measures

(1) To develop a clinical screening tool for identifying older women with back pain who are likely to have VFs. The output of this aim is a simple clinical checklist likely to consist of self-reported data and data from physical examination. The primary evaluative measure will be the accuracy of the Vfrac tool as represented by the sensitivity and specificity. The aim is for sensitivity and specificity of > 80% to justify subsequent evaluation in a definitive trial. Data from the baseline questionnaire, the physical examination and spinal radiograph will be used.

(2) To produce an online version of the combined predictors for easy use as a clinical tool (Vfrac) to identify which older women with back pain are likely to have a VF and, therefore, needs a radiograph. The output of this aim is a web-based online version of the clinical checklist (see primary objective).

(3) To model the cost-effectiveness of Vfrac based on follow-up of the participants to identify if a future definitive cluster randomised controlled trial is appropriate. The output of this aim will be an estimate of likely cost-effectiveness and a list of sources of variation that can be tested in a pilot as part of a future application for funding. Data at follow-up by self-report plus from GP electronic records will be used.

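### The stated cost-effectiveness contrast, Vfrac against care without it, cannot show whether selecting women by the tool is worthwhile compared with radiographing all

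*Protocol article*

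**What the plan says.** The Outline section, after the study flowchart, gives the tool's output as a "binary assessment of (1) yes—this person needs a spinal radiograph, or (2) no radiograph needed". Objective 3, under Objectives and outcome measures, is "To model the cost-effectiveness of Vfrac based on follow-up of the participants to identify if a future definitive cluster randomised controlled trial is appropriate".

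The section Analysis—modelling cost-effectiveness describes two sides. For the tool: "A modelling approach will be used to estimate the cost-per-quality adjusted life year (QALY) if Vfrac is implemented in the NHS". For the difference between the sides: "Data from the literature will be used to model the likely difference in change in QALYs between any future control and intervention arms". Because the cohort is not randomised, diagnosis and treatment without the tool cannot be measured, and the section continues: "It is, therefore, necessary to explore alternative scenarios using expert opinion". The next sentence says what the experts are asked: "Opinion of experts in the fields of primary care, osteoporosis and care of the elderly will be obtained on likely patient pathways in the absence" (that is, without the tool). The rest of the section covers uncertainty, model validity and the NHS perspective. It names no further comparator.

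In the cohort itself the tool selects nobody. According to the Outline, an appointment is made for each participant "to have a physical examination in secondary care followed by a lateral thoracic and lateral lumbar radiographs" on the same day. The report goes to her GP, and she is followed up at 3 months by questionnaire and GP records.

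**The concern.** A tool that sorts women into radiograph and no radiograph earns its value from the radiographs it avoids, set against the fractures it leaves unfound. A comparison with care without the tool does not measure that. If few older women with back pain are radiographed now, almost any policy that radiographs more of them will find more fractures and gain QALYs, however well or badly it selects. A favourable ratio against care without Vfrac could therefore arise where selection is clearly efficient. It could equally arise where radiographing the whole group would cost less and find more.

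The plan's own reasoning makes this relevant. Background and rationale attributes the unfavourable £30,000 per QALY of the previous screening tool mainly to low prevalence in unselected women, and Vfrac responds by moving to a group in which fractures are expected to be more common. Higher prevalence improves the case for Vfrac against doing nothing. It also weakens the case for selecting at all. What is at stake is the economic evidence on whether to proceed to a definitive trial.

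**Working it through.** **Inputs.** From Sample size: prevalence p of 12-20%, sensitivity Se and specificity Sp of 80-95%, N = 1633. From Objectives and outcome measures: a target above 80% for each. Not in the documents: T, the cost per woman of applying the checklist and examination; R, the cost per woman of the radiographs; D, the downstream cost per fracture found; and the QALY gain per fracture found.

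**The plan's own figure.** N = 1.96² × Se × (1 − Se) / 0.05² / p. At Se = 0.85 and p = 0.12 this is 3.8416 × 0.1275 / 0.0025 / 0.12 = 1632.7, rounded up to 1633. It reproduces. The article gives no figure for the economic model.

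**Vfrac against radiographing all, at 80%/80%.** The share sent for a radiograph is q = Se × p + (1 − Sp)(1 − p). Radiographs avoided = N(1 − q). Fractures missed = N(1 − Se)p.

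| p | q | Fractures present | Radiographs avoided | Fractures missed | Avoided per missed |
|---|---|---|---|---|---|
| 12% | 0.096 + 0.176 = 0.272 | 196 | 1189 | 39 | 30.3 |
| 15% | 0.120 + 0.170 = 0.290 | 245 | 1159 | 49 | 23.7 |
| 20% | 0.160 + 0.160 = 0.320 | 327 | 1110 | 65 | 17.0 |

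Radiographs avoided per fracture missed fall as prevalence rises. Sample size states that true prevalence is probably above the source figures.

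**Higher accuracy.** At 95%/95%, q = 0.158 at p = 12% and 0.230 at p = 20%. Radiographs avoided are 1633 × 0.842 = 1375 and 1633 × 0.770 = 1257. Fractures missed are 1633 × 0.05 × 0.12 = 10 and 1633 × 0.05 × 0.20 = 16.

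**When selection fails.** For the detection step, Vfrac costs T + qR per woman and radiographing all costs R. Vfrac costs more and finds fewer if T/R > 1 − q:
- at 80%/80%: 0.728, 0.710 and 0.680 for p = 12%, 15% and 20%;
- at 90%/90%: 0.804, 0.780 and 0.740.

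With downstream costs the condition becomes T > R(1 − q) + D(1 − Se)p, so any positive D makes domination harder to reach.

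**Illustration, with all costs and QALY gains assumed.** Take 80%/80%, 0.02 QALY per fracture found, no downstream cost, and no detection as a stand-in for care without Vfrac.
- *Case A:* p = 20%, R = £30, T = £30. Vfrac: (30 + 0.32 × 30) / (0.16 × 0.02) = £12,375 per QALY. Radiograph all: 30 / (0.20 × 0.02) = £7,500. Vfrac is dominated.
- *Case B:* p = 12%, R = £60, T = £5. Vfrac: (5 + 0.272 × 60) / (0.096 × 0.02) = £11,104 per QALY. Going on to radiograph all: (60 − 21.32) / (0.024 × 0.02) = £80,583 per extra QALY. Selecting by the tool is the efficient choice at any threshold between these two ratios.

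The two-sided comparison returns about £12,000 and £11,000 for opposite conclusions. With D = £500 added, Vfrac in case A is no longer dominated: radiographing all then costs £13,000 per extra QALY over Vfrac. The answer therefore turns on inputs that the model would have to supply.

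**The case against.** The strongest reply is that this is a condensed article. It describes how one hard input, care without the tool, will be obtained, and it does not present a closed list of strategies. A full health-economic plan could contain more. Care without Vfrac is also a coherent comparator for a future two-arm trial. Objective 3 promises only an estimate of likely cost-effectiveness and a list of sources of variation, and accuracy above 80% is a separate condition.

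Part of this stands. A further document may add comparators, and the model informs the trial decision without settling it alone. But the article does state a contrast. The alternative scenarios are introduced because care without the tool cannot be observed, so they concern that same comparator.

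Three stronger readings are tempting, and the documents do not support them.
- *Vfrac is dominated.* No cost is given. The tool is meant to be a simple checklist, and a cheap one may well be efficient. The sums also leave out radiation and radiology capacity, which favour selection.
- *The cohort directly observes a radiograph-all policy.* Participants answer a postal invitation and give two consents. Women with a recent full spinal X-ray, or judged unsuitable by their GP, are excluded. The tool is meant for women who present with back pain. Uptake cannot be learned from women who all attended for a radiograph.
- *Radiographing all finds every fracture.* The reference is the ABQ reading by a trained clinician researcher, whereas the GP acts on the routine report. If that report picks up a share r of ABQ fractures, regardless of the tool's result, the gap of 39-65 shrinks to r times that.

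**Conclusion.** The point holds in limited form. The contrast in Analysis—modelling cost-effectiveness mixes the value of radiographing more women with the value of choosing among them. It cannot show that choosing by the tool is worthwhile compared with radiographing all.

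The trade-off left unexamined is large at the accuracy target: about 1110-1189 radiographs avoided against 39-65 fractures missed in 1633 women. At 95%/95% it is about 1257-1375 against 10-16. These figures assume the plan's prevalence range and take the ABQ reading as the reference. The break-even of 0.68-0.73 of a radiograph's cost also assumes 80%/80% accuracy and no downstream costs. Whether Vfrac lies above or below it cannot be told from the documents.

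Nothing here says which women should be radiographed in practice; radiographing all is needed only as a comparator. The point warrants a change to the modelling plan. It does not threaten the accuracy objective or the conduct of the cohort.

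**What to change.** In Analysis—modelling cost-effectiveness, add a spinal radiograph for all women over 65 with back pain as a third modelled strategy. Report a fully incremental analysis across no Vfrac, Vfrac and radiograph all. Charge the Vfrac strategy with the cost of administering the checklist and examination, and report the break-even value of that cost.

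Take fracture prevalence, the yield of the routine radiograph report and the post-radiograph pathways from the cohort. Treat radiograph uptake, and the yield in women who present to their GP, as assumptions varied in sensitivity analysis.

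Report the three-strategy result as part of the evidence for objective 3. A fixed go/no-go rule need not be attached to it.

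The cost is some extra modelling, which the study timeline places after data collection. No new patients or procedures are needed. The result may be less favourable to the tool.

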## Access to data

Direct access will be granted to authorised representatives from the sponsor and host institution for monitoring and/or audit of the study to ensure compliance with regulations. Patients will be asked for permission to share anonymised data beyond the immediate project team. The data will be deposited at the University of Bristol Research Data Repository (as controlled data). A metadata record will be published openly by the repository and this record will clearly state how data can be accessed.

## Quality assurance procedures

The study will be monitored or audited in accordance with the currently approved protocol, good clinical practice, relevant regulations and standard operating procedures of the sponsor. A Vfrac study Steering Committee, with terms of reference as per the funder’s guidelines, and will meet twice per year between 1st January 2018 and 30th June 2021. The. The Vfrac management team will meet monthly.

## Ethical and regulatory considerations

The investigator will ensure that this study is conducted in accordance with the principles of the Declaration of Helsinki. The chief investigator will ensure that this study is conducted in accordance with relevant regulations and with good clinical practice.

## Publication policy

Upon study completion, a report will be prepared for the funding body. The results will be published in peer-reviewed journals and presented at scientific meetings. Arthritis Research UK and the University of Bristol’s open access policies for publication of peer-reviewed papers will be followed.

The chief investigator and co-applicants will be involved in reviewing drafts of the manuscripts, abstracts, press releases and any other publications arising from the study. Authors will acknowledge that the study was funded by Arthritis Research UK. Authorship will be determined in accordance with the ICMJE guidelines and other contributors will be acknowledged.

A poster summarising the results will be sent to all GPs involved with the study to display in their waiting area. Any patients who give us their email address will be sent a copy of this poster. A summary of the results will also be posted on the study webpage: http://www.bristol.ac.uk/translational-health-sciences/research/musculoskeletal/rheumatology/research/vfrac-study.html

## Conclusion

If successful, this planned cohort study will result in a simple checklist ready for testing within the NHS to identify which older women with back pain should have a spinal radiograph as they are at high risk of having a VF. Correct identification of women with VFs will allow them to have medications and other treatments to reduce their risk of future fracture by half [24]. This is likely to have substantial impacts on both NHS healthcare costs (by reducing hip fracture costs, for example) as well as improving quality of life for older people.
